### ***Data collection (Appendix A)***

After screening for eligibility, patients will be given information sheets regarding the main aspects of the trial and information will be discussed with the research nurse before informed consent is obtained. All data is collected by research team members blinded to group assignment. Patient demographics and body mass index are recorded. Cumulated opioid consumption data and time to first morphine rescue are extracted from PCA pump. At 2-hour, 4-hour, 8-hour, 12-hour, 24-hour, 48-hour and 72-hour post-extubation, pain scores at rest and on coughing are quantified using NRS from 0 to 10. Zero represents no pain at all while 10 points represents the worst pain ever. The patients are asked to rate the overall satisfaction to pain management on a verbal analogue scale (0=worst possible, 100=best possible) at the predefined points. Any nausea and vomiting, and use of rescue antiemetics are documented. The Chinese validated QoR-15 will be completed at baseline (preoperatively) and postoperatively at 24-hour and 72-hour after extubation. The SF-MPQ-2 and Brief Pain Inventory will be used to evaluate the CPSP at 3-month, 6-month and 12-month after surgery.

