### ***Anaesthesia and Interventions***

All patients receive standard cardiac surgery monitoring. General anaesthesia is induced with midazolam 0.01-0.05 mg/kg, fentanyl 2-5 mcg/kg, and rocuronium 0.5-1 mg/kg to facilitate intubation. Anaesthesia is maintained with sevoflurane and propofol infusion, targeting a Bispectral Index of 40-60. ITPB is performed after anaesthesia induction with the patient in lateral decubitus positioning. Intraoperative opioids (fentanyl and morphine) will be administered at the discretion of the anaesthesiologist. The postoperative analgesia protocol was identical in both study groups, including patient-controlled analgesia (PCA) morphine protocol for 72 hours after surgery, oral analgesics (paracetamol 1g every 6 hours, dihydrocodeine 30mg three times a day), and on-demand antiemetics (intravenous ondansetron 4mg every 8 hours). Rescue analgesics on top of the protocol regimen can be prescribed as needed. Upon ICU admission, propofol infusion is stopped to facilitate weaning from ventilator using Adaptive Support Ventilation (ASV), which adjusts the ventilation parameters depending on the patient's lung mechanics and effort. Pain will be assessed regularly in ICU and on the ward. Upon extubation, pain scores are assessed at 2-hour, 4-hour, 8-hour, 12-hour, 24-hour, 48-hour and 72-hour. Patients receive PCA morphine for moderate to severe pain. Nausea, vomiting and rescue antiemetics are documented.

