***Outcome measures***

Though acute pain is identified as an important predictor for the development of CPSP, advanced pain management strategies have failed to reduce the overall incidence of CPSP, suggesting a complex underlying mechanism. Evidence has demonstrated that pain-related functional interference and patient-reported outcomes, such as quality of recovery, might be associated with the development of CPSP. Thus, the primary outcome of this study is the Quality of Recovery (QoR-15) score at 24 hours after extubation. QoR is recommended for patient's comfort after surgery, and is highly valid and reliable patient-centred outcome measure.

Secondary outcomes include Numerical Rating Scale (NRS) pain scores at 2-hour, 4-hour, 8-hour, 12-hour, 24-hour, 48-hour and 72-hour after extubation, patient satisfaction with pain management and postoperative morphine consumption at the above time points, the time for first morphine rescue (in minutes), intraoperative opioids consumption (converted into morphine equivalence), duration of mechanical ventilation, length of stay in ICU and hospital, side effects associated with opioids such as postoperative nausea and vomiting (PONV), incidence of CPSP at 3-month, 6-month and 12-month, and pain interference measured with Short-Form McGill Pain Questionnaire-2 (SF-MPQ-2) and Brief Pain Inventory (BPI) Interference Scale at 3-month, 6-month and 12-month after surgery.

CPSP is defined as persistent pain after surgery that was not present before surgery or that had different characteristics, and other possible causes of pain are excluded. Participants reported CPSP will further be assessed on the severity and impact of chronic pain based on the recommendations by the Initiative on Methods, Measurement, and Pain Assessment in Clinical Trials (IMMPACT), including the SF-MPQ-2 to assess the sensory pain qualities and affective components, and the BPI to assess the interference of pain with physical functioning.

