## Appendix A

The following medical and surgical data during the hospital stays will be extracted from electronic record:

1. Patient demographics (age, gender, EuroScore)
2. Type of surgery
3. Duration of surgery and duration of cardiopulmonary bypass
4. ASV time to spontaneous breathing
5. Episodes of nausea and vomiting, and use of rescue antiemetics
6. Length of ICU and hospital stay

|                     |           | STUDY PERIOD    |             |             |             |              |              |              |              |         |         |
|---------------------|-----------|-----------------|-------------|-------------|-------------|--------------|--------------|--------------|--------------|---------|---------|
|                     | Enrolment | Post-allocation |             |             |             |              |              |              |              |         |         |
| TIMEPOINTS          | Baseline  | 2h extubate     | 4h extubate | 6h extubate | 8h extubate | 12h extubate | 24h extubate | 48h extubate | 72h extubate | 3-month | 6-month |
| ENROLMENT:   |           |                 |             |             |             |              |              |              |              |         |         |
| Eligibility screen  | X         |                 |             |             |             |              |              |              |              |         |         |
| Informed consent    | X         |                 |             |             |             |              |              |              |              |         |         |
| Demographic data    | X         |                 |             |             |             |              |              |              |              |         |         |
| Comorbidity data    | X         |                 |             |             |             |              |              |              |              |         |         |
| EuroScore           | X         |                 |             |             |             |              |              |              |              |         |         |
| Allocation          | X         |                 |             |             |             |              |              |              |              |         |         |

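### Opioid consumption and time to first rescue are read from the PCA pump, while rescue analgesics are allowed off the pump with no listed item to record them

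*Protocol*

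**What the plan says.** Four parts of the protocol bear on this.

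- **Source of the data** (Data collection): "Cumulated opioid consumption data and time to first morphine rescue are extracted from PCA pump". No other source is named for either endpoint.
- **What patients may receive** (Anaesthesia and Interventions): the regimen is the same in both groups and is described as "including patient-controlled analgesia (PCA) morphine protocol for 72 hours after surgery", with scheduled paracetamol and dihydrocodeine by mouth. The section then adds: "Rescue analgesics on top of the protocol regimen can be prescribed as needed". It gives no drug class, route or recording rule for this rescue.
- **What is analysed** (Outcome measures): the secondary outcomes include "postoperative morphine consumption at the above time points", which run from 2 h to 72 h after extubation, and the time to the first morphine rescue. Opioids given during surgery are a separate outcome: "intraoperative opioids consumption (converted into morphine equivalence").
- **What is listed for recording**: Data collection says "Any nausea and vomiting, and use of rescue antiemetics are documented". Appendix A opens its list with "The following medical and surgical data during the hospital stays will be extracted from electronic record"; that list and the assessment schedule also include rescue antiemetics. None of the three includes rescue analgesics.

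**The concern.** A pump log holds only what the pump delivered. Rescue given beyond the PCA regimen is by description outside it, so the stated source cannot show it. If some of that rescue is opioid, two things follow. The consumption total at that reading and every later one is too low for that patient. And if the off-pump dose came first, the recorded time to first rescue is too long, or the patient appears never to have needed rescue.

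The Introduction names early postoperative analgesia among the secondary aims, and these two endpoints measure it directly. Off-pump rescue is given because pain is not controlled, which is what the block is meant to change. Unequal use between arms is therefore plausible even with blinded prescribers, since different pain leads to different prescribing.

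A second, smaller matter concerns timing. PCA is timed from surgery and the readings are timed from extubation, so as written the last reading falls after protocol PCA has ended.

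**Working it through.** The protocol gives no figure for morphine use, rescue use or ventilation time, so there is no stated number to reproduce. The sample size rests on QoR-15 alone (8 points, SD 12) and does not enter.

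**1. Consumption.** For one patient let M be the morphine delivered by the pump and R the off-pump rescue opioid in morphine equivalents, with R ≥ 0.

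- Opioid actually received beyond the scheduled oral drugs: M + R.
- Recorded under the stated rule: M.
- Error for the patient: M − (M + R) = −R, which is zero or an undercount.
- Error in the difference between arms (control minus block): −(mean R in control − mean R in block).

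The last line is zero if mean off-pump opioid is equal in the arms, whatever its level. It shrinks the measured benefit of the block if controls receive more, and enlarges it if they receive less. The documents give neither mean, so neither size nor sign can be fixed.

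Scheduled dihydrocodeine is also off the pump, but the planned dose is the same in both groups, so it matters less for the comparison.

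**2. Time to first rescue.** The time by any route is the smaller of the first pump time and the first off-pump time. The recorded time is the first pump time alone. The error is zero when the pump comes first and positive when it does not.

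**3. Is rescue recorded elsewhere?** Data collection, the electronic-record list and the assessment schedule all name rescue antiemetics and none names rescue analgesics. The schedule's row for postoperative morphine consumption names no source, so the sentence in Data collection is the only stated rule.

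**4. The two clocks.** The anaesthesia section says "Upon ICU admission, propofol infusion is stopped to facilitate weaning from ventilator", so extubation follows surgery. Let V be the hours from the end of surgery to extubation. A reading t hours after extubation falls t + V hours after surgery and lies within protocol PCA only if t + V ≤ 72.

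- t = 72 requires V = 0, so the last reading is outside for any patient extubated after surgery.
- t = 48 requires V ≤ 72 − 48 = 24. Methods expects patients to leave the ICU within 24 h of surgery, so this should usually hold.
- The protocol does not give V. The values below are assumed.

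| V (assumed) | Last reading, hours after surgery | Hours outside PCA | Share of the 48–72 h interval |
|---|---|---|---|
| 4 | 76 | 4 | 4/24 = 17% |
| 6 | 78 | 6 | 6/24 = 25% |
| 12 | 84 | 12 | 12/24 = 50% |
| 24 | 96 | 24 | 24/24 = 100% |

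These are hours without protocol PCA, not amounts of morphine missed. They lead to error in two ways. Morphine may be given off the pump after PCA ends, which is step 1 again. Or PCA access may stop at differing times after extubation, so that the 72 h total covers 72 − V hours on the pump and V varies between patients or arms.

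**The case against.** The strongest reply is that endpoint and source match. The outcomes are worded in terms of morphine, PCA is the stated route for moderate to severe pain, and reading PCA morphine from the pump is coherent; counting all opioids would be a broader endpoint. This stands in part, and it is a reason to keep PCA-only morphine as a reported quantity. It does not dispose of the point. Data collection speaks of opioid consumption, morphine given off the pump would still be postoperative morphine, and a total that omits opioid given for failed pain relief is a weak measure of analgesic need.

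The second reply is that the protocol does not say the rescue is opioid. That stands. Non-opioid rescue would leave both pump-based endpoints as they are, so the undercount is possible, not certain.

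The third is that non-recording is argued from silence. Appendix A is not a complete list, blinded staff record data in the ICU and on the wards, and a case report form may capture rescue drugs. A reader might infer that off-pump rescue will go unrecorded altogether; the documents do not support that. They support the narrower statement that the named source for these two endpoints is the pump and that no listed item covers the rest.

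The fourth is that the clock mismatch may be loose wording. The protocol times the primary outcome from extubation in Outcome measures and calls it postoperative in the sample size section, so it does interchange the two. That is a fair reading, and one phrase would settle it. A reader might also infer that the 72 h total is wrong for every patient. It is not: if no morphine is given after PCA ends, the pump total is what the patient received, though over a shorter period on the pump.

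**Conclusion.** The point holds as a minor one. The stated source rule leaves out any opioid rescue given off the pump and can mistime the first rescue. Because the rule is written into the protocol, this is more than missing detail. It affects two secondary endpoints; QoR-15 at 24 h and the sample size are unaffected.

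The conclusion assumes that at least some off-pump rescue is opioid. For a bias between arms it assumes also that such rescue differs by arm. Neither is established by the documents, and the bias is nil if rescue is non-opioid or equal in the arms. It would be tempting to say that the benefit of the block will be understated, or to put a loss of power or a milligram error on it. The documents support neither: they give no rescue rate, dose, morphine SD or extubation time, and the trial was not sized on these endpoints.

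The clock mismatch is true as written but secondary. It concerns only the 72 h reading, provided extubation is within 24 h of surgery, and it may be no more than wording.

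**What to change.** - Add a rescue-analgesic item to Appendix A (drug, dose, route, time), taken from the electronic record that is already being read.
- Define postoperative opioid consumption as PCA morphine plus off-pump rescue opioid in morphine equivalents, as is already done for intraoperative opioids. PCA-only morphine may still be reported alongside.
- Define time to first rescue as the time of the first opioid rescue by any route.
- State that PCA runs to 72 h after extubation, or make 48 h after extubation the last consumption reading.

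The cost is one row in Appendix A, a few sentences and a little extra extraction. Extending PCA adds V pump hours per patient; stopping at 48 h loses one of seven consumption readings.

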### ***Statistics and sample size calculation***

Sample size was calculated using G\*Power software version 3.1.9.3 (Kiel University, Kiel, Germany), based on the QoR-15 score at 24 hours postoperatively — the primary outcome. The minimum clinically important difference (MCID) for the QoR-15 score is eight points, and the typical standard deviation (SD) ranges from 10 to 16. Assuming a two-sided type I error of 0.05, type II error of 0.2, and a population variance of 144 (SD = 12), a sample size of 36 per group is required. Allowing for a 20% dropout rate as a result of loss to follow up after patients discharge, a total of 96 patients (48 patients per group) will provide 80% power to detect a mean difference of  $\geq 8$  points in the QoR-15 score at 24 hours between the two groups.

All outcomes will be analyzed and reported on an intention-to-treat basis, with patients analyzed according to their randomized group regardless of protocol adherence. A secondary per protocol analysis will be conducted for patients who do not adhere fully to the study protocol. Given the repeated measures of pain scores over time, which are correlated,

Generalised Estimating Equation (GEE) models will be used to assess the time effects of postoperative analgesia. Categorical data will be reported as counts and percentages. Continuous variables will be presented as mean (standard deviation) or median (interquartile range), depending on normality assessed using the Shapiro-Wilk's test. Between-group comparison will be conducted using the independent sample *t*-test for parametric data and Mann-Whitney U test for nonparametric data. Categorical variables will be compared using the Chi-square test. Data analyses will be performed using SPSS 27.0 (IBM Corp, Armonk, NY), and GEE modelling will be conducted using Stata V.14 (Statam College Station, Texas, USA), with a Gaussian distribution, identify-link function, exchangeable correlation structure, and robust standard errors. A P-value of  $<0.05$  will be considered statistically significant, without adjusting for multiple comparisons.

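### The secondary per-protocol analysis is worded for patients who did not adhere, the reverse of a per-protocol set; only this supportive analysis is affected

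*Protocol*

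**What the plan says.** Two consecutive sentences in the Protocol, section Statistics and sample size calculation, define the analysis populations. The first sets the main one: "All outcomes will be analyzed and reported on an intention-to-treat basis, with patients analyzed according to their randomized group regardless of protocol adherence". The second adds the supportive one: "A secondary per protocol analysis will be conducted for patients who do not adhere fully to the study protocol".

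No other section of the Protocol mentions a per-protocol set, describes who belongs to it, or says that non-adherent patients are removed from any analysis.

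**The concern.** A per-protocol analysis is confined to patients who received what they were allocated and followed the plan. It is reported beside ITT to show whether the result changes once deviators are set aside. The sentence attaches the analysis to the deviators themselves.

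An analyst who followed it literally would compare the two arms among patients picked out by events after randomisation. Such a comparison loses the protection of randomisation, rests on few patients, and says nothing about the effect in those who were treated as planned. The intended check on the ITT result would be lost.

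This is not a detail that a statistical analysis plan would normally supply. The Protocol makes a positive statement, and it is the wrong one. A later plan with a conventional per-protocol set would contradict the Protocol; a plan that followed the Protocol would carry the error forward.

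**Working it through.** **1. The two sentences side by side.** The ITT sentence keeps every patient in the randomised group whatever the adherence, so non-adherers are already included there. The natural counterpart is a sentence saying who is left out of the second analysis. Instead, the second sentence says whom the analysis is for, and names the non-adherers. The population named and the name of the analysis cannot both be right.

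**2. The Protocol's own sample size, to show that it does not depend on this sentence.** Inputs, all from Statistics and sample size calculation: difference 8 points ("The minimum clinically important difference (MCID) for the QoR-15 score is eight points"), SD 12, two-sided alpha 0.05, power 80%.

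- n per group = 2 × (1.960 + 0.842)² × 12² / 8² = 2 × 7.85 × 2.25 = 35.3, rounded up to 36. This agrees with "a sample size of 36 per group is required".
- By the noncentral t distribution, 36 per group gives 79.7% power and 37 gives 80.8%, so the stated figure is reproduced within tolerance.
- Dropout: 36 / (1 − 0.20) = 45 per group. The Protocol plans 48, slightly more.

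Correcting the per-protocol sentence changes none of these figures.

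**3. Size of the set as worded and of the set as corrected.** The Protocol gives no non-adherence rate, so f is an assumption, taken from 5% to 30% and equal in both arms. Non-adherers per arm = 48 × f; adherers per arm = 48 × (1 − f). Power for 8 points at SD 12 is Φ(8 / (12 × √(2/n)) − 1.96) under the normal approximation. The t-test figure, at n rounded to a whole number, follows in brackets.

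| Assumed f | Non-adherers per arm | Power | Adherers per arm | Power |
|---|---|---|---|---|
| 5% | 2.4 | 11% (7%) | 45.6 | 89% (89%) |
| 10% | 4.8 | 18% (15%) | 43.2 | 87% (86%) |
| 20% | 9.6 | 31% (29%) | 38.4 | 83% (82%) |
| 30% | 14.4 | 43% (40%) | 33.6 | 78% (77%) |

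Rounded, the set as worded holds about 2 to 14 per arm and the adherers' set about 34 to 46.

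**4. Sensitivity to dropout.** If the full 20% allowance were also lost, 48 × 0.8 = 38.4 per arm would remain. The non-adherers would then number 38.4 × 0.05 = 1.9 to 38.4 × 0.30 = 11.5 per arm, and the adherers 38.4 × 0.70 = 26.9 to 38.4 × 0.95 = 36.5. The contrast is the same. The Protocol ties this loss to the period after discharge ("Allowing for a 20% dropout rate as a result of loss to follow up after patients discharge"), so it may bear less on the 24-hour QoR-15 score than on the later outcomes.

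Power describes precision only. The selection problem in step 1 would remain at any size of the non-adherent group.

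**The case against.** The strongest reply is that the term per protocol has a settled meaning. Placed straight after a sentence on ITT, the wording can be read as a loose way of saying that an analysis will be done to deal with non-adherent patients, or that it will be done only if there are any. On that reading a competent analyst would run the usual analysis and nothing would go wrong. This largely stands as an account of intent: a drafting slip is the likeliest explanation. It does not rescue the text, because nothing else in the Protocol states the intended population and the reader is left to guess.

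A reader might go further and infer that the trial will compare deviators, or that its main conclusion is at risk. The Protocol supports neither inference. The analysis is labelled secondary, all outcomes are analysed by ITT, and the sample size does not rest on this sentence.

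It is also fair to object that the counts and power figures are illustrative. They rest on an assumed rate and an equal split between arms, which is why a range is shown and not a single value. Finally, the absence of a list of disqualifying deviations is no fault here, since a statistical analysis plan commonly supplies it.

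**Conclusion.** The point holds as an error of wording in a prespecified analysis: the population named is the complement of a per-protocol set. That conclusion needs no assumption about rates. The illustration of size (about 2 to 14 per arm as worded, about 34 to 46 per arm as corrected) assumes 5% to 30% non-adherence, equal in both arms, with all 96 patients available. The consequence is limited to one secondary analysis. It should be corrected, but it does not threaten the primary comparison.

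**What to change.** Replace the sentence with:

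> A secondary per-protocol analysis will be restricted to patients who adhered to the study protocol, analysed by randomised group, with disqualifying deviations classified before unblinding; the ITT analysis is primary.

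The list of deviations can sit in the statistical analysis plan.

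One caution concerns that list. Intraoperative remifentanil and re-operation within 24 hours might seem obvious entries, but the Methods section (Exclusion) names both as exclusion criteria for the trial. Both become known only after allocation, which Appendix A places at baseline, whereas the ITT rule keeps every randomised patient. Naming them as per-protocol deviations would settle, without saying so, whether such patients stay in the trial. The Exclusion paragraph and the ITT rule should be reconciled first; until then, neither event should be written into this sentence.

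The cost is one sentence in the Protocol. No change to the sample size, the data collection or the main analysis is needed.

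### The primary QoR-15 comparison leaves out the baseline score the trial collects, and a normality test on the data decides whether a mean difference is estimated at all

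*Protocol*

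**What the plan says.** - **Outcome.** Protocol, Outcome measures: "the primary outcome of this study is the Quality of Recovery (QoR-15) score at 24 hours after extubation".
- **Baseline.** Protocol, Data collection (Appendix A), on the QoR-15: it "will be completed at baseline (preoperatively) and postoperatively at 24-hour and 72-hour after extubation". The schedule in Appendix A also marks QoR-15 at baseline.
- **Sample size.** Protocol, Statistics and sample size calculation: "The minimum clinically important difference (MCID) for the QoR-15 score is eight points", and with "a population variance of 144 (SD = 12), a sample size of 36 per group is required". The target is a difference in means of at least 8 points, with 96 patients (48 per group) after a 20% allowance for dropout. The same section says that "the typical standard deviation (SD) ranges from 10 to 16".
- **Analysis.** The same section presents continuous variables as mean (SD) or median (IQR), "depending on normality assessed using the Shapiro-Wilk's test". The next sentence reads "Between-group comparison will be conducted using the independent sample" *t*-test for parametric data, with Mann-Whitney U for nonparametric data. No covariate, change score or separate primary analysis is given. The only model, a GEE, is introduced for the repeated pain scores; it names neither QoR-15 nor a baseline covariate.

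**The concern.** Two separate weaknesses sit in the same rule.

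First, a preoperative QoR-15 is planned for each patient, yet the stated primary comparison does not use it. To the extent that baseline predicts the 24-hour score, the unadjusted test has a larger standard error than it needs, and a chance baseline difference in a trial of 96 patients goes uncorrected in the estimate.

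Second, the rule lets the trial data choose the test. If normality is rejected, the result is presented as medians and tested by ranks. That does not estimate the mean difference on which the MCID and the power statement are built, so the trial could finish without a mean difference and confidence interval to set against its own 8-point criterion.

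This is not a gap left for a statistical analysis plan to fill. The Protocol names the tests and the criterion for choosing between them, and an analysis plan that followed it would carry the problem forward.

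**Working it through.** **Inputs from the Protocol.** Difference 8; SD 12 (cited range 10 to 16); two-sided alpha 0.05; power 80%; 48 per group; dropout 20%.

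**Assumed, not in the documents.** The correlation *r* between baseline and 24-hour QoR-15 (shown from 0.1 to 0.5), and the shape of the QoR-15 distribution.

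**1. The plan's own figure.** Normal approximation: n = 2(1.960 + 0.842)² × 144 / 8² = 35.3, so 36 per group, as stated. The noncentral *t* calculation gives 37 (power 79.7% at 36). After 20% loss, 48 × 0.8 = 38.4, so about 38 per group are evaluable. The sample size arithmetic is not the issue.

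**2. What the baseline is worth.** Residual SD = SD × √(1 − r²). The noncentrality is 8 / (residual SD × √(2/n)), with 2n − 2 degrees of freedom unadjusted and 2n − 3 with the covariate. Example for n = 38, SD 12, r = 0.5: residual SD = 12 × √0.75 = 10.39; noncentrality = 8 / (10.39 × 0.2294) = 3.36, against 2.91 unadjusted; power 91.2% against 81.8%.

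| r | Variance removed | 38/group, SD 12 | 38/group, SD 16 | 48/group, SD 12 |
|---|---|---|---|---|
| unadjusted | – | 81.8% | 57.6% | 89.8% |
| 0.1 | 1% | 82.2% | 58.0% | 90.1% |
| 0.2 | 4% | 83.3% | 59.3% | 91.0% |
| 0.3 | 9% | 85.2% | 61.6% | 92.3% |
| 0.4 | 16% | 87.9% | 65.0% | 94.1% |
| 0.5 | 25% | 91.2% | 70.0% | 96.2% |

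**3. How often the gate would switch the test.** Shapiro-Wilk at the 5% level on simulated scores:

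- Single samples of 48 from a left-skewed (reflected gamma) score: about 27% rejected at shape 12 (skewness 2/√12 = 0.58) and about 67% at shape 4 (skewness 2/√4 = 1.0).
- Whole trials of 38 per group, each arm tested, switching if either rejects: about 10% go to Mann-Whitney when scores are truly normal, and about 80% at shape 4.

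**4. What the gate does to error rates.** In the same 38-per-group trials (6,000 runs), type I error of the gated procedure is 5.4% (normal) and 5.2% (shape 4). Its power is 82.1% against 82.4% for the *t*-test under normality, and 86.5% against 82.5% at shape 4. So the gate costs no material power; what it changes is the quantity reported.

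**The case against.** - **The unadjusted comparison is valid.** In a randomized trial it is unbiased with correct type I error, its standard error already allows for chance imbalance, and it meets the planned 80% at SD 12 with 38 per group. This stands: the point is about efficiency and a fixed effect measure, not about an invalid test.
- **The correlation is unknown and could be low**, since baseline precedes cardiac surgery and the outcome comes 24 hours after extubation. This also stands. At r = 0.1 to 0.2 the gain is only 0.4 to 1.5 points.
- **Thirty-eight per group may be too few.** The Protocol attributes the 20% loss to follow-up after discharge, which should hardly touch a 24-hour endpoint. With all 48 evaluable, the gain at r = 0.3 to 0.5 is 2.5 to 6.4 points (92.3 − 89.8; 96.2 − 89.8).
- **The low power at SD 16 comes mainly from the SD.** Correct: at r up to 0.5, adjustment does not restore 80% there.
- **Shapiro-Wilk is literally tied to presentation, not to the test.** The link runs through the next sentence's split into parametric and nonparametric data. That is the natural reading, because no other criterion is offered.
- **The wording is generic and the analysis plan may refine it.** It is generic, but it is the only rule covering the primary outcome, and it states a choice rather than leaving one open.

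These points limit the size of the gain. None removes the mismatch between an 8-point mean-difference target and a rule that may not estimate it.

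**Conclusion.** The concern holds, as something that should be changed rather than a flaw that invalidates the trial.

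The part that needs no assumed correlation is the effect measure: the data decide whether the primary result is a mean difference or a rank comparison, while the trial is powered and interpreted on a mean difference. How often the switch would occur depends on the distribution of QoR-15, which the documents do not describe. It ranges from about 10% of trials under normality to about 80% under clear left skew, if each arm is tested.

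The precision forgone depends on r. At SD 12 and 38 per group it is 3.4 to 9.4 power points for r of 0.3 to 0.5 (85.2 − 81.8; 91.2 − 81.8), and 1.5 points or less for r of 0.2 or below. It is smaller if nearly all 48 per group reach the 24-hour assessment. The benefit also applies if the SD proves larger than 12, although adjustment alone would not rescue power at SD 16.

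**What to change.** In Statistics and sample size calculation, add one paragraph that sets the primary analysis apart from the generic rule:

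- A linear model of 24-hour QoR-15 on randomized group with baseline QoR-15 as covariate and robust standard errors.
- Report the adjusted mean difference with its 95% CI, whatever the Shapiro-Wilk result, and read it against the 8-point MCID.
- Keep Mann-Whitney U as a named sensitivity analysis only.
- Use the same model for the 72-hour QoR-15.

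The cost is that paragraph. Baseline QoR-15 is already scheduled, so there are no new data and no change to the sample size. It should be settled before unblinding, because choosing the model afterwards would itself be data-driven.
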